#### Allogeneic hematopoietic cell transplantation

Subjects are permitted to undergo allo-HCT at any time after salvage therapy. Quizartinib should be discontinued at least 7 days before the start of a conditioning regimen. Maintenance therapy may be given starting the earliest at day 30 and the latest at day 100 after transplant according to initial randomization.

#### Continuation therapy

All patients achieving CR are allocated according to randomization to either (a) the MRD-triggered arm or (b) the prophylactic arm receiving treatment with quizartinib. During consolidation therapy, patients allocated to the MRD-triggered arm (a) receive one cycle of HAM and are further allocated based on the MRD results assessed by flow cytometry with a cut of level of 0.1%: if the MRD is negative they remain in the MRD-triggered arm for another HAM cycle, whereas MRD-positive patients move to the prophylactic arm. All patients randomized to (b) the prophylactic arm will receive quizartinib during their two cycles of HAM therapy irrespective of MRD results (see Fig. 1).

Patients achieving MRD negativity in the MRD-triggered arm will not receive treatment during the maintenance phase. MRD-positive patients have to move to the prophylactic arm receiving quizartinib as single agent and will continue the study for up to 12 treatment cycles presenting themselves at monthly visits to assess the course of therapy. Patients in the MRD-triggered arm are attending visits in 3-monthly intervals only. During maintenance therapy, starting from cycle 2, the quizartinib dosage will be increased up to 60mg orally, if the average QTcF of the triplicate ECGs is lower than 450 ms on cycle 1, day 28. Once the dose is increased to 60mg/day, the subject may continue on this dose as long as no dose reduction is needed. In case of therapy with a strong CYP3A4 inhibitor a dose reduction to 20mg per day is required. The maintenance phase is followed by a safety follow-up of 28 days counted from the end of treatment (EOT) for all patients from the prophylactic arm. Dose modifications are listed in Tables 2 and 3.

**Table 3 Tab3:** Inclusion and exclusion criteria

**Category**	**Inclusion**	**Exclusion**
Population characteristics	- Patients with diagnosed acute myeloid leukemia according to the 2016 WHO classification. who are either • refractory to induction therapy or • relapsed after first line treatment including chemotherapy, autologous and/or allo-HCT* - Positive for FLT3-ITD (defined as a ratio of mutant to wild-type alleles of at least 0.05; measured within 4 weeks before inclusion) - Age ≥ 18 years and ≤ 75 years - ECOG performance status ≤2. - Effective contraception method.	- AML with PML-RARA or BCR-ABL1. - Patients with known active CNS leukemia. - Isolated extramedullary manifestation of AML - Clinically relevant GvHD requiring initiation of treatment or treatment escalation within 21 days prior to screening - Pregnancy and lactation. - Known or suspected active alcohol or drug abuse. - Known positivity for HIV, active HBV, HCV, or hepatitis A infection. - Severe neurologic or psychiatric disorder interfering with ability of giving informed consent. - Hyperleukocytosis (leukocytes > 30,000/μl) at the time of study entry.** - Refractoriness to platelet or packed red cell transfusions
Prior Therapies	- Discontinuation of prior AML treatment for at least • 10 days for cytotoxic agents and • 28 days for investigational drug treatment before the start of study treatment (except hydroxyurea to control hyperleukocytosis)	- allo-HCT within the previous 100 days - Prior treatment with quizartinib
Comorbidities	- Adequate renal function defined as creatinine clearance >50 mL/min (calculated using the standard method for the institution)	- Inadequate renal function. - Inadequate liver function. - Known liver cirrhosis. - History of Sinusoidal Obstruction Syndrome (SOS) - Uncontrolled hypertension. - Severe obstructive restrictive. ventilation disorder. - Myocardial infarction. - Congenital long QT syndrome. - Torsades de pointes. - Arrhythmias (including sustained ventricular tachyarrhythmia). - Right or left bundle branch block and bifascicular block. - Unstable angina. - Coronary/peripheral artery bypass graft. - symptomatic congestive heart failure (NYHA III/IV). - Cerebrovascular accident. - transient ischemic attack. - Symptomatic pulmonary. embolism. - Bradycardia defined as <50 bpms. - QTc interval >470 ms. - Uncontrolled infection. - Evidence or history of severe non-leukemia-associated bleeding diathesis or coagulopathy. - Patients with a “currently active” second malignancy other than non-melanoma skin cancer. - Severe neurologic or psychiatric disorder interfering with ability of giving informed consent.
Others	- Signed written informed consent. - Ability of patient to understand the character and consequences of the clinical trial.	- No consent for biobanking. - History of hypersensitivity to the investigational medicinal product or to any drug with similar chemical structure. - Participation in a clinical study involving an investigational drugs. - No consent for registration, storage, and processing of the individual disease characteristics.

Inclusion and exclusion criteria: The following eligibility criteria are designed to select patients for whom protocol treatment is considered appropriate.* Refractory to induction therapy is defined as no CR, or CRi, or PR (according to standard criteria) [1] after 1 or 2 intensive induction cycles of at least 7 days of cytarabine 100–200mg/m^2^ continuously or an equivalent regimen with cytarabine with total dose not less than 700mg/m^2^ per cycle and 2 days of an anthracycline (e.g., daunorubicin, idarubicin). Relapsed after first-line therapy is defined as relapsed AML (according to standard criteria) [1] after a first-line therapy including at least one intensive induction and consolidation therapy including (but not limited to) allo-HCT. **These patients should be treated with hydroxyurea according to routine practice and are only allowed to enter into the study when leukocyte counts of 30,000/μl or below are reached

*Abbreviations: CNS*, central nervous system; *ECOG*, Eastern Cooperative Oncology Group; *NYHA*, New York Heart Association; *allo-HCT*, allogeneic hematopoietic cell transplantation; *GvHD*, graft-versus-host disease; *AML*, acute myeloid leukemia

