#### Additional study procedures during salvage, maintenance therapy, and follow-up

Patients undergo efficacy and safety assessments, including monitoring of Measurable Residual Disease (MRD), bone marrow specimen collection, and blood and urine sampling before receiving the study drug and at the end of each treatment cycle. During maintenance and follow-up, trial-specific samples are taken every third month. Routine examinations (physical signs, blood values, etc.) are taken at least weekly during treatment. Patient-reported outcome questionnaires are to be completed before treatment and after the end of each treatment cycle, and additionally in 3-month intervals during maintenance and follow-up. AEs are recorded during every visit. Strong CYP3A4 inhibitors should be avoided, and strong or moderate CYP3A4 inducers must not be used.

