### Sample collection

The samples will be collected at the following time points: (i) at baseline, (ii) after salvage therapy, (iii) after consolidation therapy, (iv) after each cycle of consolidation therapy, (v) after each cycle of maintenance therapy, (vi) at the end of treatment, (vii) every 3 months during observational follow-up, and at end of study. Provided patients’ applicable informed consent is given, biological samples are stored to develop further knowledge and understanding of diagnostic, prognostic and predictive markers present in AML patients.

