For the analysis of the primary endpoint, a logistic regression model will be applied to assess the odds ratio of CR/CRi/CRh rate after salvage therapy for patients receiving Q-HAM versus matched controls not receiving Q-HAM. The null hypothesis H0: OR≤1 is tested against its alternative H1: OR>1 at a one-sided significance level of *α*=0.05. The logistic regression analysis will be adjusted for age, high-risk cytogenetics (yes/no), and CR1 duration <18 months (yes/no/not applicable due to refractory disease). Due to the adaptive nature of the trial, two separate logistic models will be fitted for the two trial stages and be combined using the inverse normal function approach. Determination of *p*-values, point, and interval estimates will take the adaptive nature of the trial into account. Concerning the secondary endpoints: EFS, OS, and RFS endpoints will be analyzed using a Cox regression model and Kaplan-Meier plots, CIR, and CID will be analyzed according to Gray 1988 [33] and via cumulative incidence plots, and quality of life will be analyzed descriptively according to the corresponding guidelines and EORTC recommendations. Safety endpoints will be analyzed descriptively. Analyses of the primary and secondary endpoints will be based on the full analysis population (all randomized patients with treatment groups assigned in accordance with the randomization, regardless of the treatment actually received (intention to treat (ITT)). For patients with incomplete follow-up, time to last follow-up date will be used as the censoring time in the analysis of time-to-event data. Otherwise, no imputation of missing data will be conducted. For the biometricians, patient treatment shall remain blinded from the time of randomization until the final database lock. The interim analysis and sample size recalculation will be conducted by an independent biometrician who is not involved in the conduct of the trial. Statistical analysis will be performed using SAS v9.4 or higher [34].

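### Monthly visits on quizartinib maintenance against 3-monthly visits off it can date relapse later in the MRD-triggered arm and modestly tilt the randomized EFS/RFS comparison towards that arm

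*Protocol article*

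**What the plan says.** Continuation therapy sets the visits. Patients on single-agent quizartinib maintenance "will continue the study for up to 12 treatment cycles presenting themselves at monthly visits to assess the course of therapy". This covers the prophylactic arm and the MRD-positive patients who move to it. For the rest, "Patients in the MRD-triggered arm are attending visits in 3-monthly intervals only". Under Long-term follow-up, everyone is seen 3-monthly once treatment has ended.

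The section on additional study procedures gives two sampling rules. One places MRD monitoring, "bone marrow specimen collection, and blood and urine sampling before receiving the study drug and at the end of each treatment cycle". The other reads "During maintenance and follow-up, trial-specific samples are taken every third month" and makes no distinction by arm. It adds: "Routine examinations (physical signs, blood values, etc.) are taken at least weekly during treatment". Sample collection lists its time points as "v) after each cycle of maintenance therapy, (vi) at the end of treatment, (vii) every 3 months during observational follow-up, and at end of study", which is per cycle in maintenance and 3-monthly only afterwards.

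Under Efficacy endpoints, relapse can be established from marrow, from blasts returning in the blood, from new extramedullary disease or from Auer rods. EFS also counts failure of salvage therapy. The Discussion names EFS as the endpoint of the randomized comparison, and Design describes the trial as open-label. The statistics section says "EFS, OS, and RFS endpoints will be analyzed using a Cox regression model and Kaplan-Meier plots", with patients analysed as randomized.

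**The concern.** When relapse is noticed at a visit, its recorded date is the visit date and not the date on which it became detectable. The longer the interval between visits, the later the recorded date. If one arm is seen monthly and the other every 3 months, the less-watched arm can appear to relapse later although nothing differs biologically. A Cox or Kaplan-Meier analysis of recorded dates carries that difference into the hazard ratio.

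Here the less-watched patients are those off quizartinib, so the error favours the MRD-triggered strategy, and its direction is known in advance. It concerns the only randomized question in the trial. At the planned size, about 22 patients per arm would be at risk of relapse (0.55 × 40), so even a modest shift would be hard to separate from a real effect.

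**Working it through.** The article gives no figure for the randomized EFS/RFS comparison, so there is none to reproduce.

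**Inputs from the article**
- Visit interval: 1 month on maintenance for up to 12 cycles, 3 months off it, and 3 months for all after end of treatment.
- Minimum follow-up: 730 days, taken as 24 months.
- 40 patients per arm and an assumed remission rate of 0.55, hence 22 responders per arm and 1 − 0.55 = 45% salvage failures.

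**Assumptions not in the article**
- Exponential RFS with median 6, 9 or 12 months, and a true hazard ratio of 1.
- 20% of RFS events are deaths with exact dates; 80% are relapses.
- Relapses found between visits: 0% or 50%.
- MRD-triggered patients who move to monthly visits: 0% or 40%.
- Unequal visits run from month 0 to month 12 after remission, with one cycle counted as one month.
- For EFS, salvage failures are dated alike in both arms.

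**Delay.** A relapse arising uniformly between visits waits half an interval on average. That is 3/2 = 1.5 months against 1/2 = 0.5 month, so the extra delay is 1 month.

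**Effect on the hazard ratio.** Relapse times were rounded up to the next visit and a Cox model with Breslow ties was fitted to very large samples (1,000,000 patients per run). Values above 1 favour the MRD-triggered arm (prophylactic versus MRD-triggered).

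| Median RFS (months) | RFS, worst case | RFS, 50% between visits and 40% moving | EFS, worst case | EFS, 50% between visits and 40% moving |
|---|---|---|---|---|
| 6 | 1.11 | 1.03 | 1.06 | 1.01 |
| 9 | 1.06 to 1.07 | 1.01 | 1.03 | 1.01 |
| 12 | 1.04 | 1.01 | 1.02 | 1.00 to 1.01 |

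The worst case means that every relapse is found at a visit and nobody moves to monthly visits. If only the between-visit share is raised to 50%, RFS gives 1.05, 1.03 and 1.02. Where a range is shown, separate runs differed in the second decimal.

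**Effect on false positives.** A log-rank test with 44 responders was run 2,000 times at a nominal 2.5% per side. In the worst case with a median of 6 months, it favoured the MRD-triggered arm in 6.3% of runs and the prophylactic arm in 1.1%. The other settings gave 3.3% to 4.0% in favour of the MRD-triggered arm. The simulation standard error is about 0.4 points, so differences among those settings should not be interpreted.

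**Marrow schedule.** If the every-third-month sentence governs, trial marrow and MRD samples are equally timed in both arms. Visits, and the chance of noticing blood blasts or extramedullary disease, still differ. If the per-cycle wording governs, marrow timing differs as well. Neither reading gives fully equal ascertainment, and the first leaves less bias than the worst case above.

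**The case against.** Several points limit this.

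- A visit is not a relapse assessment. If the every-third-month rule governs marrow, much of the imbalance disappears. This stands, and it is why the bias is possible but not certain.
- MRD-positive patients of the MRD-triggered arm move to monthly visits but are analysed as randomized. Routine care after end of treatment will also find some relapses between visits. Both stand, and the milder columns reflect them.
- Salvage failures, dated alike in both arms, dilute EFS. This stands; EFS shows about half the RFS effect.
- Dating rules and sensitivity analyses often sit in an analysis plan that is not shown. This is fair for the choice of model. It does not answer the unequal visits and the conflicting sampling rules, which the article itself states.
- The trial closed early with 11 patients, so 22 responders per arm will not occur. This reduces the practical stakes to how any comparison of the arms is analysed and reported.

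A reader might also infer more than the text supports. Spurious RFS hazard ratios of about 1.14, 1.09 and 1.07 arise only if monthly visits last all 24 months, but they end after at most 12 cycles. Weekly blood values might seem to widen the gap, but whether that rule extends to maintenance, with its monthly visits, is unclear. Unequal recording of adverse events is a thin point, because spontaneous reports are recorded too and safety is analysed descriptively.

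**Conclusion.** The concern holds in a limited form. The article sets different visit frequencies for patients on and off quizartinib maintenance and contradicts itself on sampling in that phase. Followed as written, it can date relapse later in the MRD-triggered arm. It does not establish that this must happen.

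The worst-case bias is a hazard ratio of about 1.11 for RFS and 1.06 for EFS at a median RFS of 6 months. It shrinks with a longer median and is about 1.00 to 1.03 under the milder assumptions. The median RFS, the share of relapses found between visits and the share moving to monthly visits are all assumed. The model also starts unequal visits at remission. Relapses during consolidation, when both arms are assessed at the end of each cycle, would dilute the effect further. OS does not depend on visit dates and is unaffected.

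**What to change.** 1. Reconcile Continuation therapy, the section on additional study procedures and Sample collection into one relapse-assessment schedule, with marrow, MRD and blood assessments for relapse at the same months in both arms.
2. For the randomized comparison of EFS and RFS, assign relapses in both arms to a common 3-monthly grid, or fit an interval-censored proportional hazards model. At the least, pre-specify one of these as a sensitivity analysis beside the Cox model on actual dates.

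The cost is a small loss of precision from coarser dates and a little more analysis work. No extra visits are needed. After early closure, the second step still applies to any reported comparison of the arms.

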### Treatments and study procedures

#### Salvage therapy

All patients are randomized upfront and receive one cycle of backbone salvage therapy with a standard HAM regimen. In patients aged 18–60 years, one cycle of cytarabine 3g/m^2^ every 12 h will be administered intravenously on days one to three, and in patients older than 60 years of age, cytarabine will be administered at a reduced dosage of 1g/m^2^ bidaily on days one to three. Mitoxantrone will be administered irrespective of age group, intravenously at a dosage of 10mg/m^2^ on days two and three. All patients will receive in addition 40 mg of quizartinib orally on days 1 to 28. If on day 28 no hematological recovery has occurred, and according to the first bone marrow examination no CR is achieved, quizartinib may be given until day 42 and a second remission control can be done if medically justified until day 42. If a therapy with a strong CYP3A4 inhibitor is initiated, a dose reduction of quizartinib to 20mg per day will be initiated. Dose modifications in case of toxicities are described in Tables 1 and 2.

**Table 1 Tab1:** Dose reduction or interruption of quizartinib

Nonhematological events grade 3 related to quizartinib and persisting > 48 h without resolution to ≤ grade 2	Dosing will be interrupted for up to 14 days. If the AE resolves to ≤ grade 1 within 14 days, the subject may resume dosing at the reduced dose of at least 50%.
Grade 4 toxicity at least possibly due to study drug	Treatment will be discontinued
Myelosuppression CRp or CRi	Dose may be reduced without interruption if the following criteria are met: Subject has received a minimum of 2 cycles of ASP2215, platelets < 25 × 10^9^/L and/or ANC ≤ 0.5 × 10^9^/L, marrow blasts < 5%, no evidence of extramedullary disease, further dose reduction is permitted if dosing 1 full cycle at the reduced dose has not resulted in the desired hematologic recovery.

*Abbreviations: AE*, adverse event; *ANC*, absolute neutrophil count; *CRi*, complete remission with incomplete hematologic recovery; *CRp*, complete remission with incomplete platelet recovery

**Table 2 Tab2:** Dose reduction or interruption of quizartinib in case of QTcF prolongation

QTcF >480 ms ≤500 ms	The dose of quizartinib will be reduced by at least 50%without interruption of dosing. Following dose reduction, the quizartinib dose may be resumed at the previous level in the next cycle if the QTcF has decreased to within 30 ms of baseline or <450 ms.

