QTcF >500 ms	Quizartinib dosing will be interrupted for up to 14 days. • If QTcF returns to within 30 ms of baseline or <450 ms within 14 days, quizartinib administration may be resumed at a reduced dose. If QTcF >500 ms occurs during the Induction or Consolidation Phases, and if no cause other than quizartinib can be identified, then during the maintenance phase, the dose of quizartinib cannot be escalated to 60 mg/day.
QTcF >500 ms or >60 ms change from baseline, and Torsade de pointes or polymorphic ventricular tachycardia or signs/symptoms of serious arrhythmia	Quizartinib dosing will be permanently discontinued.

*Abbreviations: QTcF*, corrected QT interval by Fredericia

Subjects who experience QT interval prolongation of more than 480 ms corrected for heart rate (QTcF) will undergo dose interruption and/or reduction of quizartinb and will be monitored closely by ECGs, performed twice weekly for the first week of the QTcF prolongation and then weekly thereafter until the QTcF prolongation is resolved (Table 2). QTcF prolongations higher than grade 3 according to the National Cancer Institute Common Terminology Criteria for Adverse Events (CTC AE) will be recorded as adverse events of special interest (AESI) including the Investigator’s assessment of seriousness, causality, and a detailed narrative.

In the event of significant toxicity grade 3 or 4, dosing must be interrupted, delayed, and/or reduced by at least 50% [20]. In the event of unresolved or severe toxicities, administration will be interrupted and in case of multiple toxicities, dose modification should always be based on the worst toxicity observed. Quizartinib will be discontinued in case of non-hematological grade 4 toxicities including grade 4 QTcF prolongation.

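### The maintenance step-up to 60 mg is not reconciled with Tables 1 and 2 for patients whose quizartinib was reduced or interrupted during maintenance cycle 1

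*Protocol article*

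**What the plan says.** The Continuation therapy section sets the maintenance dose step, which takes effect with the second cycle. It reads: "the quizartinib dosage will be increased up to 60mg orally, if the average QTcF of the triplicate ECGs is lower than 450 ms". The ECGs in question are those of day 28 in the first cycle, and no other condition is attached. The following sentences deal with staying on 60 mg once it has been reached and with strong CYP3A4 inhibitors. The paragraph ends with a cross-reference: "Dose modifications are listed in Tables 2 and 3".

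The dose-modification tables themselves stand under Salvage therapy.

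- Table 2, QTcF above 480 and up to 500 ms: the dose is cut by at least half without interruption. Afterwards "the quizartinib dose may be resumed at the previous level in the next cycle", provided QTcF is back within 30 ms of baseline or below 450 ms.
- Table 2, QTcF above 500 ms: dosing stops for up to 14 days. On recovery to the same criterion it may restart at a reduced dose. The row adds a bar with this trigger: "If QTcF >500 ms occurs during the Induction or Consolidation Phases, and if no cause other than quizartinib can be identified". Its stated consequence is that escalation to 60 mg is ruled out in maintenance.
- Table 1, persisting grade 3 non-hematological toxicity related to quizartinib: dosing stops for up to 14 days and, on resolution to grade 1 or lower, may restart at a reduced dose.
- Table 3 lists the inclusion and exclusion criteria. It contains no dose modifications.

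**The concern.** The escalation sentence looks at QTcF on one day. It does not ask what dose the patient was taking then, or whether dosing had just been changed because of QTcF or another toxicity. Tables 1 and 2 govern exactly those patients and describe a different next step. The bar in Table 2 shows that the authors meant some QTcF events to block 60 mg. It names the phases before maintenance, however, and not the cycle that immediately precedes the escalation decision.

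What is at stake is safety and uniform dosing. The Background reports that QT prolongation led to dose reduction in the earlier programme, with grade 3 prolongation in 35% of patients at 200 mg. It gives no rate for 40 to 60 mg. Two investigators applying this text in good faith to the same patient could arrive at different doses.

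**Working it through.** No figure in the plan needs reproducing; the check sets the rules side by side, case by case.

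**Case 1: QTcF above 500 ms before maintenance, no cause other than quizartinib.** The escalation sentence taken alone would allow the step. Table 2 forbids it, and the Continuation therapy section refers to Table 2. Settled, although the sentence does not mention the bar.

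**Case 2: QTcF above 480 and up to 500 ms in maintenance cycle 1, dose cut, then below 450 ms on day 28.** For an event in cycle 1, the next cycle in Table 2 is cycle 2, which is also where escalation starts. A value below 450 ms satisfies both rules. Table 2 permits a return to the former level. The escalation sentence directs an increase with a ceiling of 60 mg. Not reconciled.

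**Case 3: QTcF above 500 ms in maintenance cycle 1, then below 450 ms on day 28.** Table 2 allows a restart at a reduced dose, and its bar does not name this phase. The escalation sentence directs an increase. Since the interruption may last 14 days, one that begins on or after day 14 (28 − 14) could still be running on day 28, so the qualifying value might even be obtained off drug. Not reconciled.

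**Case 4: dose cut or interrupted for grade 3 non-hematological toxicity in maintenance cycle 1.** Table 1 restarts at a reduced dose. The escalation sentence carries no toxicity condition, and the section's cross-reference omits Table 1 and names the eligibility table instead. Not reconciled.

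**Size of the gap in case 2.** Let D be the maintenance starting dose. The section does not state D. After a cut of at least half, the day 28 reading is taken on D/2 or less. The escalation ceiling is then:

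- relative to the dose at the reading: at least 60 / (D/2) = 120/D;
- relative to the dose at which QTcF was prolonged, which is also where Table 2 stops: 60/D.

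| Assumed D | Dose at reading | 120/D | 60/D |
|---|---|---|---|
| 40 mg (the salvage dose carried over) | 20 mg or less | at least 3 | 1.5 |
| 30 mg (illustrative) | 15 mg or less | at least 4 | 2 |

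The ratio 60/D exceeds 1 for every D below 60 mg, and speaking of an increase up to 60 mg implies a start below that. The two ceilings therefore differ whatever D is; only the size of the gap depends on the assumption.

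**How many patients.** The plan allocates 40 patients to each arm and assumes a remission rate of 0.55, so about 40 × 0.55 = 22 patients randomized to the prophylactic arm could enter continuation, plus MRD-positive patients moving over from the other arm. Only those who reach maintenance and have a reduction or interruption in cycle 1 are affected. The document gives no rate for that.

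**The case against.** The best defence is that the Continuation therapy section cites Table 2, so an investigator should read the escalation sentence subject to the table's event-specific rules. On that reading 60 mg is a ceiling and not a target: going from 20 mg back to 40 mg is an increase within it and complies with both places. Cases 3 and 4 then turn largely on silence about how an earlier reduction affects later escalation, and a journal article may leave that to the full protocol. The table reference is an evident slip, since the Salvage therapy section cites Tables 1 and 2 for the same purpose; read that way, Table 1 does apply in maintenance. The term Induction in Table 2 is a matter of labelling, because the Study monitoring section also uses it for the first treatment phase.

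Much of this stands. Case 2 can be read consistently, and the labelling point carries no weight. But the latitude in the ceiling comes with no instruction on how to use it, and nothing says that Table 2 prevails. In case 3 a bar that lists the earlier phases invites the inference that a maintenance event does not count, while the same row restarts dosing at a reduced level. That is more than omitted detail: the stated rules lead to different doses.

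A reader might go further and infer that a single ECG reading is the only gate, or that any patient just reduced or interrupted for QTcF prolongation qualifies for 60 mg. The document does not support either. The gate is the mean of triplicate ECGs, at one time point. Table 2 already bars patients with quizartinib-attributed QTcF above 500 ms in the earlier phases. Grade 4 non-hematological toxicity and QTcF prolongation with serious arrhythmia lead to discontinuation, so those patients cannot be escalated.

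**Conclusion.** The point holds as an internal inconsistency in the dosing text, confined to patients whose dose was reduced or interrupted during maintenance cycle 1. For them the escalation sentence and Tables 1 and 2 do not yield one answer, and the cross-reference that should join them names the wrong table. It should be corrected because it bears on safety and needs only a change of wording.

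The threefold and 1.5-fold differences rest on a 40 mg maintenance start, which is an assumption; the existence of a gap needs only a start below 60 mg. The number of patients affected is unknown and probably small: the Trial status section reports 11 patients included and a decision to close early. The primary endpoint is untouched, because remission is assessed after salvage. A reader might also infer that the randomized comparison of the two continuation strategies is compromised. Nothing in the document shows or sizes such an effect. No view is taken here on which dose rule is right.

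**What to change.** Reconcile the escalation sentence in Continuation therapy with Tables 1 and 2, so that one stated rule covers patients whose dose was reduced or interrupted in maintenance cycle 1, whether for QTcF or for other toxicity. State whether a QTcF above 500 ms during maintenance counts towards the bar on 60 mg. Mention the Table 2 bar in the escalation sentence itself. Change the cross-reference from Tables 2 and 3 to Tables 1 and 2. Stating the maintenance starting dose in the same place would make the former level in Table 2 unambiguous. The content of the clinical rule is for the sponsor to set.

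The cost is a wording amendment and a notice to sites, for which the plan already has a newsletter. It adds no procedures or patients and changes no analysis. Depending on how the sponsor reconciles the rules, some patients may receive a different maintenance dose from the one a site would now choose.
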